### Sample size

The sample size was calculated using the WINPEPI (PEPI-for-Windows) [21] software, based on the main hypothesis of the study. According to a relevant study published by Lacroix et al. [8], where a group of health older adult subjects performed unsupervised exercises obtaining a reduction of 0.37 s in TUG execution time when compared to pre and post intervention with duration of 12 weeks. Considering the standard deviation of 0.84 for the IG and 1.02 for the CG observed in the study, with a statistical power of 80% and an alpha error of 5%, 101 participants in each group would be necessary. The sample will be increased by 10% to compensate for possible dropouts, leading to 111 subjects in each group (overall sample = 222 participants).

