## Methods/design

### Study design and setting

The design and conduct of this study follows the guidelines of The Standard Protocol Items “Recommendations for Intervention Trials (SPIRIT) guidelines” [13], according to the flow chart of the study showed in Fig. 1. This is a blind, randomized controlled clinical trial, using a superiority test and a 1:1 allocation ratio. The sample will be of convenience, composed of elderly subjects in a community in the city of Senhor do Bonfim, BA, northeastern region of Brazil. The protocol is reported according to the Standard Protocol Items: Recommendations for Interventional Trials (Fig. 2 SPIRIT diagram and Additional file 1: SPIRIT Checklist).

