**Table 1 Tab1:**
[figure not shown]
The schedule for data collection and outcome measurement

*CG* control group, *IG* intervention group, *CHAMPS* Physical Activity Questionnaire for Older Adults

Weight will be measured while wearing light clothing and without shoes, after emptying of the bladder, using a digital scale to the nearest 100 g. Height will be measured without shoes, with a stadiometer to the nearest 0.5 cm (model 200/5; Welmy Industria e Comercio Ltda, Sao Paulo, Brazil). Body Mass Index (BMI) will be calculated by dividing weight (kg) by the square of height (m) [15].

Functional mobility will be evaluated by the Timed Up & Go (TUG) test. This test measures, in seconds, the time taken by an subject to stand up from a standard arm chair (seat of the chair with height of 46 cm and arms with 65 cm of height), walk a distance of 3 m, at a comfortable and safe pace, turn, walk back to the chair, and sit down again. The subject wears his regular footwear and uses his customary walking aid (none, cane, or walker). Three tests will be performed with each subject in a 1-min interval, with the best performance being chosen as the final measure [16].

According to the test, an execution time of less than 10 s suggests totally free and independent individuals. Individuals who perform the test between 10 and 19 s are considered independent, and those who perform the test in 20 to 29 s are in the so-called “grey zone,” that is, demonstrating limited functional capacity and difficulties in tasks of daily living. Those who perform the test in 30 s or more tend to be totally dependent for many basic and instrumental activities of daily living [16].

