## Discussion

This is a study designed to verify whether a semi-supervised, home-based exercise program alters the functional mobility and QoL of sedentary community elderly persons when compared to a control population. This hypothesis is based on research that has already demonstrated the efficacy of physical exercise programs in terms of functional mobility [7, 22, 23] and improving the QoL of elderly people [8, 9]. However, most of these studies adopted professional supervision during the execution of exercise programs, in addition to being performed in training and/or rehabilitation centers [24–26], which is characterized as a limiting factor for the participation of elderly people, as they may have difficulties with mobility and transfer [27]. The benefits of such programs depend on the degree of adhesion to exercise, which is influenced by the intensity of pleasure and satisfaction provided [27, 28].

It has already been demonstrated in the literature that physical exercise performed at home, in addition to being the preference of elderly people, can provide important health benefits [7, 25, 29], leading to improved adherence and continuity of the exercises after the end of the proposed program [30].

One of the main characteristics of the present study is the focus on the practice of semi-supervised exercises. A strength of this study is that, after the random allocation of the participants, both groups will receive periodic home visits with the same frequency, aiming to provide the same orientation and stimuli in relation to healthy lifestyle habits. This allow the groups to acquire similar behaviors, differing only in terms of the practice of physical exercise, considering that previous studies suggest that frequent contact with the participants by telephone calls, Internet, or personal visit increases adherence of elderly people to home exercise programs [8, 29, 30].

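### The sample size uses a pre/post reduction within one exercising group (0.37 s) as the between-arm difference, so the stated 80% power rests on an unstated assumption that controls do not improve

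*Protocol article*

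**What the plan says.** The Sample size section of the protocol article relies on one cited study. It reports that a group of healthy older adults "performed unsupervised exercises obtaining a reduction of 0.37 s in TUG execution time when compared to pre and post intervention", over 12 weeks, so the reduction is described as a comparison of before with after. It then adds the spread: "Considering the standard deviation of 0.84 for the IG and 1.02 for the CG observed in the study". With 80% power and a 5% alpha error it arrives at 101 per group, raised to 111 for dropout (222 in total). It gives no control-group change and no between-group difference from that study, and it does not say that controls are assumed to stay the same.

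The trial itself compares arms. Study design and setting describes a trial "using a superiority test and a 1:1 allocation ratio", and the Statistical analysis section plans an independent-samples t test between groups. The primary outcome is change in TUG from baseline to 3 months.

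The controls are not left without contact. They attend the same talk and receive the leaflets (Randomization and allocation concealment) and have weekly telephone contact (Achieving retention). The Discussion counts it as a strength that "both groups will receive periodic home visits with the same frequency". TUG is measured at both assessments as the best of three attempts (Clinical evaluation).

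**The concern.** A superiority test between arms is powered by the intervention-arm change minus the control-arm change. The 0.37 s is described as the first of these two terms only. The two coincide when the control change is exactly zero. Any improvement in controls, whether from contact, advice or familiarity with the test, is subtracted from 0.37 s; any worsening is added to it.

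The stated power is therefore conditional on something the protocol does not state. When the result is read, and above all if it is not significant, the claimed 80% will be part of how the trial's sensitivity is judged. That figure should belong to the comparison that is actually tested.

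**Working it through.** **Inputs (Sample size section):** effect 0.37 s; SDs 0.84 (intervention) and 1.02 (control); power 80%; alpha 5%, sidedness not stated; 101 per arm.

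**Step 1: reproduce the stated figure.** With 0.37 s as the between-arm difference and a two-sided test:

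n = (1.960 + 0.842)² × (0.84² + 1.02²) / 0.37² = 7.851 × 1.746 / 0.1369 = 100.1, rounded up to 101 per arm.

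This matches. The other readings tried do not:
- one-sided 5%, two-sample: 79 per arm
- paired, one group: 41 (SD 0.84) or 60 (SD 1.02)

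So the pre/post reduction was entered as the difference between arms.

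**Step 2: power at 101 per arm if controls change.** The control changes are assumptions, because the documents give none. The intervention arm is taken to improve by 0.37 s, and 0.84 and 1.02 are taken as the SDs of the analysed variable. SE = √(1.746/101) = 0.1315 s. The noncentrality is the difference divided by the SE, and power comes from the noncentral t with 200 degrees of freedom. The last column uses the formula in step 1.

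| Control change | Between-arm difference | Noncentrality | Power, 101 per arm | n per arm for 80% |
|---|---|---|---|---|
| worsens 0.05 s | 0.42 s | 3.19 | 89% | 78 |
| none | 0.37 s | 2.81 | 80% | 101 |
| improves 0.05 s | 0.32 s | 2.43 | 68% | 134 |
| improves 0.10 s | 0.27 s | 2.05 | 53% | 188 |
| improves 0.15 s | 0.22 s | 1.67 | 38% | 284 |
| improves 0.20 s | 0.17 s | 1.29 | 25% | 475 |

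If all 111 per arm were retained, the last four powers would be 72%, 57%, 42% and 27%.

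**Step 3: how far this depends on what the SDs are.** The section does not say whether 0.84 and 1.02 are SDs of change or of TUG at one time point. If they are SDs of TUG values and the baseline-to-final correlation is r, the SD of change is the stated SD × √(2(1 − r)).
- r = 0.7 (assumed): factor √0.6 = 0.775, SE 0.1018. A t test on change then has 95% power for 0.37 s, 88% for 0.32 s and 75% for 0.27 s.
- r = 0.5 (assumed): factor 1, so the table above applies unchanged.
- r below 0.5: power is lower than in the table.

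**Step 4: a baseline-adjusted analysis, which the protocol does not plan.** If the SDs are of TUG values, the factor is √(1 − r²). For a difference of 0.27 s:
- r = 0.5: SE 0.1139, noncentrality 2.37, power 66%
- r = 0.7: SE 0.0939, noncentrality 2.88, power 82%

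**The case against.** The strongest reply is that nothing in the article shows that controls will improve. They are told only to keep up their daily activities and follow advice on healthy habits; the leaflets cover food, hydration and sleep. Best-of-three scoring at each assessment may also limit any practice gain. This stands in part: it means that a shortfall cannot be demonstrated, but it does not turn a within-group change into a between-arm difference.

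Second, if the SDs are of TUG values and r is about 0.7, a change-score t test still exceeds 80% power with a control improvement of 0.05 s. That is correct, and it is why the table in step 2 is conditional. The relief disappears if the SDs are of change or if r is 0.5 or lower, and the section does not say which case applies.

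Third, the cited study evidently had a comparator, since an SD is quoted for a control group, so its between-arm contrast might be close to 0.37 s. That is possible, but it cannot be checked from the article, which describes the figure only as a pre/post reduction.

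A reader might go further in three ways that the documents do not support:
- *The trial is underpowered.* No control change is given, and worsening would raise power above 80%.
- *The calculation contains an arithmetic error.* It does not; the stated number follows exactly from the inputs.
- *The SDs are too small because they come from healthy older adults while this trial allows a walking aid.* The walking-aid wording ("uses his customary walking aid (none, cane, or walker") belongs to the test procedure, not to eligibility, and no figure in the documents supports a particular larger SD.

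**Conclusion.** The point holds as a wrong input. A reduction described as pre/post within one exercising group was used as the difference between arms, and the exact reproduction of 101 per arm shows it. The stated 80% power applies to the superiority test if controls show no change. Power is higher if they worsen and lower if they improve, provided the intervention arm improves by 0.37 s and the SDs are those of the analysed variable.

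On those terms an assumed control improvement of 0.05 to 0.20 s takes power from 68% down to 25%, and a worsening of 0.05 s takes it up to 89%. The size of any real shortfall cannot be settled from the documents, because they give neither the control change nor the kind of SD.

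**What to change.** Rewrite the Sample size paragraph; no further enrolment is required.

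1. State the condition openly, for example: *101 per arm gives 80% power (two-sided 5%) for a between-arm difference of 0.37 s with SDs 0.84 and 1.02, assuming no improvement in the control group.*
2. Say whether the SDs are of TUG change or of TUG values at one time point.
3. If the cited study provides a between-arm difference in change, use it in place of 0.37 s and give the resulting power at 101 per arm.
4. Report power over a range of control change, as in the table above, for the between-group analysis actually planned.
5. If a baseline-adjusted analysis is adopted, treat it as a separate change to the Statistical analysis section and report its power over a range of r rather than at one favourable value.

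The cost of items 1 to 4 is one paragraph and a look back at the cited study. The stated power may become less favourable. Item 5 is a change of method with its own justification to write.

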### Outcome measures

#### Primary outcome

The expected primary outcome is the change in the functional mobility of the elderly involved in the study, verified through the mean time in minutes for the TUG test, compared at the baseline and after the 3 months’ post-intervention period.

#### Secondary outcomes

The expected secondary outcomes for the subjects involved in this study will be the change in QoL verified by the WHOQOL-OLD questionnaire and the improvement in the level of physical activity measured using the CHAMPS, compared at the beginning and after the post-intervention period of 3 months. Feasibility of the protocol will be determined by the number of eligible elderly people recruited and retention and adherence rates to the home-based exercise program. The retention rate will be defined as the percentage of subjects who completed the protocol. Adherence will be defined as the percentage of exercise sessions attended by those who were randomized to the IG. Adherence to the home-based exercise program will be recorded using attendance records (recorded by the study physicians and physiotherapists) and participant exercise diaries (recorded by the participant). The proportion of subjects distributed between the CG and the IG will be 1:1, according to the randomization process.

### Data monitoring and quality control

Systematic training of five assistants will be carried out exclusively for evaluations, and training of ten assistants will be performed for home monitoring of elderly people, five of whom will visit the IG and five of whom will visit the CG. The distribution of the number of participants to be evaluated and the number of domiciles to be visited will be done in an equivalent way among the research assistants.

### Achieving retention

Once the subject is officially registered in this trial, both in the CG and in the IG, the researchers involved in the study will make every effort to avoid possible sample losses. A number of strategies will be adopted such as weekly telephone contact; home visits every 15 days and an emergency telephone number to report any changes in the physical and/or psychological condition. In case a subject abandons the trial, this subject must be replaced by another one, remembering that in the sample calculation a sample loss of 10% in each group was considered. Adherence to the exercise protocol will be verified through the weekly records that will be filled by the participants themselves, with the help of their relatives, and will be certified by the assistants during the home visits.

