### Randomization and allocation concealment

All subjects involved in the study, before randomization, will participate in groups of 12 elderly in a 40-min talk with explanations on the evaluation and intervention procedures and will receive educational leaflets containing guidelines on healthy habits related to food, hydration, and sleep hygiene. The subjects in the IG will be informed that they will follow the guidelines of healthy habits of life and a program of home-based physical exercise. For this program, they will participate in theoretical-practical training concerning adequate accomplishment of the exercises and will receive a booklet, developed by the researchers, that contains illustrative and written guidelines on the method of performing the exercises, and a diary to register the frequency of exercise on a weekly basis.

After the explanatory meeting with all subjects, the main investigator will enroll the subjects of the study and request the randomization. A researcher from the same department, not involved in the trial, will prepare the group allocation after explanatory meeting and baseline assessment. Randomization will be computer based and carried out at a 1:1 ratio according to a random sequence generated by the Research Randomizer (https://www.randomizer.org/), generating two groups, control group (CG) and intervention group (IG: semi-supervised, home-based exercise program). Consecutively numbered, sealed, opaque envelopes containing group allocation will be prepared by the same researcher not involved in the trial. The concealed envelopes will be securely stored and will be opened in sequence to reveal group allocation (CG or IG).

The researchers, after making sure that the participants will be able to properly perform all the proposed exercises, will guide the family members to help the participants and stimulate their practice. Any change in the physical or mental condition of the participants should be communicated by telephone to the research team. Participants in the CG will be informed that they should only continue their daily living activities and follow the guidelines of healthy living habits.

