### Statistical analysis

The principle of intention-to-treat analysis will be respected. For missing data, we will perform a sensitivity analysis, through simple imputation, using the mean of the variables. Student’s *t* test for numerical variables and Pearson’s chi-square test for categorical variables will be applied to verify whether the randomization process generated two groups of subjects (CG and IC) with homogeneous clinical and demographic characteristics before intervention, thus avoiding a possible selection bias. To test the normality of the data, an analysis of the study histogram, mean and median, standard deviation, skewness, and kurtosis will be performed and for its confirmation, we will use the Shapiro-Wilk normality test. With a normal distribution of variables, parametric statistics will be used, and intragroup comparisons will be made using the Student’s *t* test for paired samples; the intergroup comparisons will be performed using the Student’s *t* test for independent samples. If there is no normal distribution of the variables, the corresponding non-parametric tests will be used. For the analysis of the groups by age, as will be done with more than two groups, we will use the one-way analysis of variance (ANOVA) for parametric distribution or Kruskal-Wallis for non-parametric analysis. The significance level established for all analyses will be *p* < 0.05 and all statistical procedures will be analyzed and processed using the Statistical Package of the Social Sciences SPSS 21.0 software (IBM® SPSS version 21, IBM, Armonk, NY, USA).

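### The rule that a participant who abandons the trial must be replaced conflicts, in its ordinary meaning, with the promised intention-to-treat analysis, and the planned dropout allowance makes it unnecessary

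*Protocol article*

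**What the plan says.** All places are in the protocol article.

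- **Achieving retention.** The scope is set by "Once the subject is officially registered in this trial, both in the CG and in the IG", so the text concerns people who already belong to an arm, not screening failures. The rule is mandatory: "In case a subject abandons the trial, this subject must be replaced by another one". The sentence goes on: "remembering that in the sample calculation a sample loss of 10% in each group was considered".
- **Statistical analysis.** "The principle of intention-to-treat analysis will be respected". On missing values: "For missing data, we will perform a sensitivity analysis, through simple imputation, using the mean of the variables". The main between-group comparison is an independent-samples t test, or its non-parametric counterpart.
- **Sample size.** 101 per group are required. "The sample will be increased by 10% to compensate for possible dropouts", which gives 111 per group and 222 in all.
- **Randomization and allocation concealment.** Allocation is concealed in numbered opaque envelopes taken in order. No procedure is given for a replacement participant.
- **Secondary outcomes.** Retention is part of the feasibility assessment: "The retention rate will be defined as the percentage of subjects who completed the protocol". The set of people over whom the percentage is taken is not stated.

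**The concern.** Intention-to-treat keeps every randomised person in the allocated arm. To replace one person by another ordinarily means that the first no longer counts. If the rule is followed in that sense, membership of each arm depends on something that happened after randomisation, and the comparison of Timed Up & Go (TUG) change loses the protection that randomisation gave it.

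This differs from ordinary missing data. A leaver who stays in the randomised set is visible as a missing outcome, can be sought for the final assessment, and is covered by the planned imputation. A leaver who has been swapped out may disappear from all three. The retention percentage would then also lack a clear denominator.

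A later analysis plan could not fully repair this, because replacement is carried out during recruitment and changes who is enrolled. The trial status section says that recruitment is still open, so the rule may already have been applied.

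**Working it through.** **1. The plan's sample size.** Inputs from the sample size section: difference 0.37 s, SDs 0.84 and 1.02, power 80%, alpha 5% (taken as two-sided).

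n per arm = (1.960 + 0.842)² × (0.84² + 1.02²) / 0.37² = 7.849 × 1.746 / 0.1369 = 100.1, rounded up to 101. The stated figure is reproduced. A one-sided test would give 79, so two-sided is the right reading.

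Inflation: 101 × 1.10 = 111.1, stated as 111. Dividing by 0.9 would give 112.2, rounded up to 113. The gap is too small to matter here.

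**2. Is replacement needed at the planned loss?** Average SD = √(1.746 / 2) = 0.934. With 10% loss, 111 × 0.9 = 99.9, or about 100 completers per arm.

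Power = Φ(0.37 / (0.934 × √(2/100)) − 1.960) = Φ(0.840) = 79.96%, against 80.3% at 101. The allowance does its job without replacement.

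**3. What the rule would add.** If leavers were replaced until 111 per arm completed:

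- at 10% loss, 111 / 0.9 = 123.3, so 124 randomised per arm (13 extra);
- at 20% loss, 111 / 0.8 = 138.75, so 139 per arm (28 extra).

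Power with 111 completers per arm would be 83.9%, more than the design asks for.

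**4. Possible readings of the rule, set against the other sections.**

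- *The leaver is dropped and the newcomer takes the same arm.* This breaks intention-to-treat and bypasses the concealed sequence.
- *The leaver is dropped and the newcomer takes the next envelope.* The sequence is respected, but intention-to-treat is still broken and the depleted arm is not necessarily refilled.
- *The leaver is kept and the newcomer is extra.* This is compatible with intention-to-treat, but no section says it.
- *Replacements come out of the 10% surplus.* The sample size is then coherent, but whether the leaver is analysed remains open.

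No reading is both stated in the article and consistent with all its sections.

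**5. Size of bias.** The documents give no dropout rate by arm and no link between leaving and outcome, so any figure rests on assumptions. Suppose that loss is informative only in the intervention arm and that leavers there improve g seconds less than completers. The completer contrast is then shifted by loss × g:

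- 10% loss: g = 0.20, 0.37 or 0.84 s gives 0.020, 0.037 or 0.084 s (5%, 10% or 23% of 0.37 s);
- 20% loss: the same g gives 0.040, 0.074 or 0.168 s (11%, 20% or 45%).

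A second model takes a correlation of 0.3 to 0.5 between the tendency to leave and a worse change, with an SD of about 0.93. It gives correlation × SD × φ(z)/(1 − loss), where z is the normal quantile that cuts off the lost fraction: about 0.055 s (10% loss, 0.3) to 0.164 s (20% loss, 0.5).

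Neither formula contains a term for replacement. Both describe informative dropout in one arm, and the same shift would arise if leavers were simply missing from the t test.

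**The case against.** The strongest reply is that recruiting an extra person is compatible with intention-to-treat if the leaver is still analysed as allocated. The protocol nowhere says that leavers' data are discarded, and it does state intention-to-treat and plan imputation. This stands in part: the conflict lies in the ordinary meaning of the word and in the silence around it, not in an explicit order to delete anyone. But the text never says that leavers are kept, and imputation as a sensitivity analysis does not bring them into the main test.

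Several stronger inferences are tempting, and the documents do not support them:

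- *The trial becomes a comparison of completers.* That follows only if replaced people leave the analysis set, which is not stated.
- *Replacements are placed in the leaver's arm, outside the sequence.* The article does not say so; a newcomer could take the next envelope.
- *Replacements are willing completers who favour exercise.* Nothing selects them for completion, they may leave too, and the rule covers both arms.
- *The rule itself causes a bias of 0.055 to 0.164 s, or 15 to 44% of the target.* That range describes assumed one-arm informative dropout. Comparable loss among controls would cancel part of it, and the article does not say whether its SDs are of change or of final values.
- *The same loss is counted twice.* The sentence mentions the 10% allowance, so replacements may be meant to come from it. What can be said is that replacement is unnecessary at the planned loss.

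It is also fair that the rule concerns a person who abandons the trial, not one who merely stops exercising. Because removal is allowed at any time, some leavers cannot be reassessed under any rule.

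**Conclusion.** The point holds as a conflict between a mandatory operational rule and the stated analysis principle, and it should be fixed before recruitment ends. It rests on the ordinary meaning of replacement, on the rule's application after allocation, and on the absence of any statement on how leavers are analysed or newcomers allocated. It does not depend on any bias figure.

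What can be quantified is that the rule is not needed at 10% loss, where about 100 completers per arm and about 80% power for 0.37 s remain. If leavers are in fact swapped out, the arms are selected on a post-randomisation event. The direction and size of the resulting bias cannot be determined from the document.

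**What to change.** Delete the replacement sentence and state that:

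- randomised participants are not replaced, and the 10% inflation is the only allowance for loss;
- those who stop the programme or leave the trial are invited to the 12-week assessment where they consent;
- all randomised participants are analysed in their allocated arm;
- retention is computed over all randomised participants.

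Deletion alone does not remove bias from missing outcomes. Following up leavers is the part that can reduce it.

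If replacements have already been enrolled, keep both the leaver and the added participant in the analysis as randomised, and report how many there were and how each was allocated.

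The cost is a short amendment and somewhat fewer completers if loss exceeds 10%. At 20% loss, for example, 111 × 0.8 is about 89 per arm, and power is Φ(0.37 / (0.934 × √(2/89)) − 1.960) = Φ(0.68), or about 75%. If that matters, the target can be raised openly for everyone, with each new participant taking the next envelope.
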